| (e) | Details of procedure and methodology proposed to be used (300 words) including description of the potential risks and benefits, exclusion and Inclusion criteria outcome measures, statistical analysis:  ***Patient population:*** *Covid-19 positive symptomatic cases either non-severe or severe category*  ***Intervention:*** *Two therapeutic interventions for non-severe category and three for severe category as described below*  ***Comparator:*** *Parallel arm design, compared among other interventional arm in same category*  ***Outcomes:*** *Clinical and laboratory improvements in 72 hours of treatment*  **Patient population-**  Patients diagnosed with SARS-CoV-2 infection after positive reverse-transcriptase–polymerase chain reaction (RT-PCR) assay.  **Inclusion criteria:**   1. Age ≥18 years at time of participation in the study 2. Laboratory (RT-PCR) confirmed infection with SARS-CoV-2 3. Symptomatic (severe or non-severe) Covid-19 disease 4. Willingness of study participant to accept randomization to any assigned treatment arm   **Exclusion criteria:**   1. Use of medications that are contraindicated with Lopinavir/Ritonavir, Hydroxychloroquine/Chloroquine, or Ribavirin and that cannot be replaced or stopped 2. Patient already on antiretroviral therapy with Lopinavir-Ritonavir based regimen or on Hydroxychloroquine/Chloroquine or on Ribavirin 3. Any known contraindication to test drugs such as retinopathy and QT prolongation 4. Known allergic reaction or inability to delivery oraly to Lopinavir-ritonavir, Hydroxychloroquine/ Chloroquine, Ribavarin 5. Pregnant or breastfeeding females 6. Receipt of any experimental treatment for 2019-nCoV (off-label, compassionate use, or trial related) within 30 days prior to participation in the present study or want to participate after enrolment   **Potential benefits:**   1. All those who participate in the trial will benefit from possible effective treatment for COVID-19 infection 2. The study will highlight the therapeutic options in management of the symptomatic patients of COVID-19 infection   **Potential risks:**  The present study will be conducted on symptomatic patients of COVID-19 attending AIIMS Rishikesh. The patients will be categorised based on severity and treatment will be allocated accordingly.  Adverse drug reactions, though not frequent may be associated with the treatment. Proper supportive management will be given to the patients at the institute.  **Methodology**:  **Flow Diagram**  Patients of COVID-19 infection - After confirmation by RT-PCR at AIIMS, Rishikesh  Screening for inclusion in trial Enrolment Excluded  ♦  Not meeting inclusion criteria  ♦  Declined to participate  ♦  Other reasons  Categorisation based on severity of patient  **SEVERE group**  **NON-SEVERE group**  Randomisation to treatment arm:  **A. Standard Treatment (ST-S)**  **B. Hydroxychloroquine + Ribavirin + ST-S**  **C. Lopinavir+ Ritonavir + Ribavirin + ST-S**  Randomisation to treatment arm:   1. **Standard Treatment (ST-NS)** 2. **Hydroxychloroquine + Ribavirin + ST-NS**  RandomisationAllocation Monitor progress of patient in 72 hours Follow-Up Patient improve- continue same treatment  Clinical evaluation- @72 hours  Improve - Continue same treatment  Progress – achieved end point and Shift to institute protocol for further treatment  Patient do not improve/ Signs of severe disease  Shift to **SEVERE group** treatment arms after randomization with new consent Analysis Analysis  **Total duration of observation**:  28 days from the time of enrolment into the study OR till patient is discharged or death whichever is longer  **Design:** Open label, Parallel arm design, stratified randomised controlled trial:  Patients will be screened for the study after diagnosis of COVID-19 infection by Microbiology team. Patients will be categorised as non-severe or severe based on predefined criteria. The patient will be enrolled in the study after a written informed consent. Since it is an exploratory trial as COVID-19 being a new disease, all patients who came under the purview of the inclusion criteria within the study period and who have consented for the study will be included. Clinical evaluations will be done by a separate investigator. Blinding will not be performed but dynamic randomization will be done. Patients will be followed up for a period of 28 days from the day of enrolment.  At the time of enrolment, demographic information will be collected from participants, and relevant data on their medical histories, comorbidities, and risk factors for severe COVID-19. It will be documented along with investigations including CBC, ECG, LFT, RFT, G6PD status.  The patients will be categorised as severe based on the following criteria:   - Confirmed pneumonia on chest imaging, SPo2 <93%, Pao_2_:Fio_2_ <300 mg Hg - Respiratory failure (need of mechanical ventilation) - Septic shock - Multiple (>2) organ dysfunction syndrome (MODS) - Liver disease (Child Pugh score ≥ C, AST>5 times upper limit) - Patients with known renal impairment (estimated glomerular filtration rate ≤30 mL/min/1.73 m2) or receiving continuous renal replacement therapy, haemodialysis, peritoneal dialysis - Other single organ failure (e.g. heart, pancreas, etc) if specific definition meets   Non-severe category includes mild and moderate disease severity category other than severe ones.  **Treatment Schedule**  **Non-severe Treatment arms (NS-group):**   \| **Treatment Arm** \| **Drug** \| \| --- \| --- \| \| A \| Standard Treatment (ST_NS_) \| \| B \| Hydroxychloroquine 400 mg twice on first day followed by 400 mg per oral daily for 10 days + Ribavirin (2.4 g orally as a loading dose followed by 1.2 g orally every 12 hours) for 10 days + Standard Treatment (ST_NS_) ^6^ \|   **Standard Treatment for non-severe cases (ST_NS_):**   1. Strict Isolation 2. Standard Precautions (Hand hygiene, Cough Etiquette, Wear surgical mask) 3. Hydration 4. Proper Nutrition 5. Supportive Pharmacotherapy (Antipyretic, Antiallergic, Cough Suppressant) 6. Treatment of Comorbid Diseases 7. Oseltamivir (75 mg BD) for patient who are tested positive for H1N1   If the patient improves clinically the same treatment will be continued. If the patient do-not improve or shows sign of severity (mentioned above) the patient will be shifted to the severity arm (S-group) of the clinical trial and again randomization will be done and enrolled after new consent only for severe group. However, if intervention falls on HCQ arm, then it will be taken as end point reached and shifted to institute treatment protocol for further management.  **Severe group Treatment arms (S-group):**   \| **Treatment Arm** \| **Drug** \| \| --- \| --- \| \| A \| Standard Treatment (ST_s_) \| \| B \| Hydroxychloroquine 400mg BD on day1 followed by 400 mg once daily + Ribavirin (2.4 g orally as a loading dose followed by 1.2 g orally every 12 hours) for 10 days + Standard Treatment (ST_s_) \| \| C \| Lopinavir(400mg) + Ritonavir (100mg) two tablets twice daily+ Ribavirin (2.4 g orally as a loading dose followed by 1.2 g orally every 12 hours) for 10 days + Standard Treatment (ST_s_)^6^ \|   **Standard Treatment for severe patients: (ST_s_)**   1. Strict Isolation 2. Standard Precautions (Hand hygiene, Cough Etiquette, Wear surgical mask) 3. Fluid Therapy 4. Supportive Pharmacotherapy (Antipyretic, Antiallergic, Cough Suppressant) 5. Oxygen supplementation (As required) 6. Invasive ventilation (As required) 7. Antibiotic agents for other associated infections (according to 2019 ATS/IDSA guidelines for non-ICU and ICU patients) 8. Vasopressor support 9. Renal-replacement therapy 10. Treatment of Comorbid Diseases 11. Oseltamivir (75 mg BD) for patient who are tested positive for H1N1   Patients will be assessed for clinical and laboratory improvements in 72 hours of treatment. In case the patient does not respond to the current treatment regimen the patient will be shifted to institute protocol for current practice of treatment.  **Timelines of investigations: Repeated at 72hrs interval**   \| Investigations \| Baseline \| Next 72hrs \| \| --- \| --- \| --- \| \| CBC \| **✔** \|  \| \| LFT \| **✔** \|  \| \| KFT \| **✔** \|  \| \| HBA1C and Blood sugar \| **✔** \|  \| \| RT-PCR for SARS-Cov-2 (until 24hrs apart twice negative) \| **✔** \|  \| \| PT/INR \| **✔** \|  \| \| Serum Electrolytes \| **✔** \|  \| \| ABG \| **✔** \|  \| \| Chest Xray \| **✔** \|  \| \| ECG \| **✔** \|  \| \| Other organ markers as per involvement \| **✔** \|  \|     **Dose Modifications:**  If any serious adverse event is recorded, the participant will be withdrawn from the trial and management will be done accordingly as per institute policy.  **Recording adverse events:**  All adverse events will be recorded in the medical records in the first instance. All adverse events will be recorded with clinical symptoms and accompanied with a simple, brief description of the event, including dates as appropriate. Each adverse event will be assessed for severity, causality, seriousness and expectedness and informed to IEC within 24hours.  **Discontinuation/withdrawal of participants:**  A participant may be withdrawn from trial treatment whenever continued participation is no longer in the participant’s best interests, but the reasons for doing so must be recorded.  Reasons for discontinuing treatment may include:   1. Unacceptable drug toxicity 2. Development of progressive disease 3. Patients withdrawing consent to further trial treatment   **Endpoints:**  **Primary endpoints:**   1. Time to Clinical recovery (TTCR)    - TTCR is defined as the time (in hours) from initiation of study treatment (active or placebo) until normalisation of fever, respiratory rate, and oxygen saturation, and alleviation of cough, sustained for at least 72 hours.    - Normalisation and alleviation criteria: 2. Fever - ≤36.9°C or -axilla, ≤37.2 °C oral 3. Respiratory rate - ≤24/minute on room air 4. Oxygen saturation - >94% on room air 5. Cough- mild or absent on a patient reported scale of severe, moderate, mild, absent 6. Time to SARS-CoV-2 RT-PCR negative in upper respiratory tract specimen 7. Time to laboratory recovery of each organ involvement   **Secondary Endpoints:**   1. All causes mortality 2. Frequency of respiratory progression  - Defined as SPO2≤ 94% on room air or PaO2/FiO2 <300mmHg and requirement for supplemental oxygen or more advanced ventilator support.  1. Time to defervescence (in those with fever at enrolment) 2. Frequency of requirement for supplemental oxygen or non-invasive ventilation 3. Frequency of requirement for mechanical ventilation 4. Frequency of serious adverse events as per AIDS table grade of severity   **Statistical analysis**:  All COVID-19 positive patients will be included in the study after informed consent. Since it is an exploratory trial as COVID-19 being a new disease, all patients who came under the purview of the inclusion criteria within the study period and who have consented for the study will be included. Data will be described as mean+ SD for most of the parameters. Comparisons of the descriptive variables of the two arms will be performed using the Wilcoxon rank sum test for continuous variables and the chi-square or Fisher’s exact test for categorical variables. Primary analysis will include all patients (Intention to treat) and sub-group populations (per-protocol).  **Ethical clearance:**  The present study deals with a new infectious disease which has no definite treatment. Current therapy is based on symptomatic treatment. The present study explores the possibilities of new drugs in SARS-CoV-2 infection. The study will be conducted after IEC approval. Written informed consent will be taken from all participants.  **Safety Outcomes**  Safety outcomes will be determined according to the division of AIDS table for grading severity of adult adverse events (<https://rsc.niaid.nih.gov/clinical-research-sites/daids-adverse-event-grading-tables>), with specific focus on the events of gastrointestinal tract, arrhythmias, myopathies. In case of serious ADRs including death, compensation will be given as per institute protocol. |

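### The shift-and-re-randomise rule and the withdraw-on-SAE rule overlap with no precedence: one ends follow-up, the other allows a second ribavirin load after possible drug injury

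*Protocol*

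**What the plan says.** All the rules stand in the Protocol, Brief description of the proposal, item (e).

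- **Shift rule** (Treatment Schedule, non-severe arms): "If the patient do-not improve or shows sign of severity (mentioned above) the patient will be shifted to the severity arm (S-group". The patient is then randomised again and enrolled in the severe group after new consent. The flow diagram says the same.
- **Only exception to the shift rule** (same paragraph): "if intervention falls on HCQ arm, then it will be taken as end point reached", and the patient goes to the institute protocol. Ribavirin is not mentioned.
- **SAE rule** (Dose Modifications): "If any serious adverse event is recorded, the participant will be withdrawn from the trial". Management then follows institute policy.
- **Severity signs** (Design): seven bullets, among them "Respiratory failure (need of mechanical ventilation) - Septic shock", multiple organ dysfunction, "Liver disease (Child Pugh score ≥ C, AST>5 times upper limit" and "Other single organ failure (e.g. heart, pancreas, etc) if specific definition meets".
- **Severe arm C**: lopinavir-ritonavir "two tablets twice daily+ Ribavirin (2.4 g orally as a loading dose followed by 1.2 g orally every 12 hours", for 10 days. Non-severe arm B has the same ribavirin schedule, and severe arm B also contains ribavirin.
- **Discontinuation/withdrawal of participants**: stopping trial treatment is permitted for, among other reasons, unacceptable drug toxicity or progressive disease.
- **Follow-up and endpoints**: observation for 28 days from enrolment, or to discharge or death if longer. All-cause mortality and need for mechanical ventilation are secondary endpoints. The primary analysis is stated as intention to treat on all patients.

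**The concern.** The two rules send the same patient in opposite directions. Under one, the patient leaves the trial; under the other, the patient stays, is randomised again and may receive more study drug. Adverse events are to be assessed for causality, but neither rule uses the result, so the investigator must choose without guidance in an open-label trial.

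Two things are at stake. The first is safety in non-severe arm B, where an organ event may be caused by the drug that severe arm C would restart. The second is the data: the choice decides who enters the severe comparison and who is still observed at day 28.

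**Working it through.** **1. The rules compared.**

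| | Shift rule | SAE rule | Discontinuation clause |
|---|---|---|---|
| Trigger | No improvement, or a listed severity sign | Any serious adverse event | Drug toxicity, progression, consent withdrawn |
| Force | Mandatory, subject to new consent | Mandatory | Permissive |
| Qualified by cause | No | No | Toxicity and progression listed separately |
| Consequence | New randomisation within the trial | Out of the trial | Off trial treatment |

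No sentence orders the first two. The third cannot do so, because it is permissive.

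**2. Overlap of the triggers.** This step assumes that serious includes life-threatening events. On that assumption, ventilation, septic shock and multiple organ dysfunction meet both triggers when they arise on treatment: 3 of the 7 severity bullets, or 4 of 7 with other single organ failure. The liver bullet overlaps only in part, since a raised AST alone need not be serious. The renal bullet concerns known impairment and is not counted.

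**3. If the SAE rule prevails.** Patients with these events leave the trial. Read literally, their day-28 status is no longer collected. Mortality and ventilation outcomes are then lost among the sickest patients, and the intention-to-treat analysis lacks data where it most needs them.

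**4. If the shift rule prevails.** A non-severe arm B patient may draw any of three severe arms. Arm A gives no more trial ribavirin. Arm B triggers the HCQ exception and also gives none. Arm C starts the ribavirin schedule again. The allocation ratio is not stated; if it were 1:1:1, one draw in three would be arm C.

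**5. Ribavirin exposure.** Inputs from the treatment tables: 2.4 g load, then 1.2 g every 12 hours for 10 days, with assessment at 72 hours. The load is taken as the first of 20 dosing times.

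- One full course: 2.4 + 19 × 1.2 = 25.2 g.
- Taken before the dose due at 72 h (0, 12, 24, 36, 48 and 60 h): 2.4 + 5 × 1.2 = 8.4 g.
- SAE rule applied at 72 h: exposure stops at 8.4 g.
- Shift to arm C, new load only: 8.4 + 2.4 = 10.8 g.
- Shift to arm C, stopped at its own 72 h check: 8.4 + 8.4 = 16.8 g.
- Shift to arm C, course completed: 8.4 + 25.2 = 33.6 g over 13 days, and 33.6 / 25.2 = 1.33.

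If the load is instead additional to 20 maintenance doses, one course is 2.4 + 20 × 1.2 = 26.4 g, the maximum is 8.4 + 26.4 = 34.8 g, and the ratio is 1.32.

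The document gives no event rates, so neither the number of patients affected nor the size of any bias can be calculated.

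**The case against.** The strongest defence is that the protocol can be read so that the rules do not collide. The SAE rule stands under Dose Modifications, and the discontinuation clause separates toxicity from progression. On that reading, drug events lead to withdrawal and disease progression to a shift. This is sensible, and the fix adopts it. The current text does not say it: the SAE rule covers any serious event, whatever its cause.

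A second defence is that several safeguards stand between a drug-injured patient and a second load. The shift needs new consent, so it is not unconditional. The toxicity clause lets the investigator stop treatment. Enrolment might also be taken to mean that the exclusions are checked again. The first two points stand and reduce the risk. The third is uncertain:

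- Exclusion 2, "Patient already on antiretroviral therapy with Lopinavir-Ritonavir based regimen or on Hydroxychloroquine/Chloroquine or on Ribavirin", would bar every arm B patient still on treatment. That fits poorly with the HCQ exception, whose apparent purpose (an inference) is to avoid repeating HCQ after arm B.
- Exclusion 3 requires a known contraindication, which a new event of unclear cause may not be.
- Exclusion 6 concerns experimental treatment before participation in this study, and these patients are already in it.

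The HCQ exception could also be read as referring to the earlier non-severe arm, which would keep all arm B patients out of the severe group. Since it follows directly on the new randomisation, that reading is the weaker one.

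A reader might take the severe-group case report form, which has a box for previous non-severe arm B treatment, as proof that ribavirin-exposed patients were expected to transfer. It is not: that form's non-severe arm B contains no ribavirin, and its severe arms differ from those in item (e).

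Finally, the detailed handling of transferred patients in the analysis may belong in an SAP. That is accepted. Whether an SAE ends observation is a protocol matter.

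**Conclusion.** The point holds: two mandatory rules with overlapping triggers have no stated order, and each causes harm if followed literally. The SAE rule cuts off follow-up in the sickest patients. The shift rule leaves open a second 2.4 g load, and at most 33.6 g against 25.2 g for one course, in a patient who may have drug injury. It should be fixed.

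Three stronger conclusions are tempting but not supported:

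- **That most patients who deteriorate meet both rules.** The overlap counts depend on an assumed definition of serious, and no frequencies are given. Even if the SAE rule took priority, the shift rule would still cover non-improvement, hypoxic pneumonia and non-serious AST rises.
- **That ribavirin exposure quadruples.** The ratio 33.6 / 8.4 = 4.0 compares a completed arm C course with stopping at 72 h. Against one planned course, the 10.8 g and 16.8 g cases are lower; only a completed arm C course exceeds it, by 33%. The second load itself is 2.4 − 1.2 = 1.2 g more than the dose due at 72 h.
- **That the protocol directs re-dosing after injury.** It permits it, given new consent and an arm C draw; it does not require it.

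**What to change.** State three rules in item (e):

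1. After an SAE the participant is withdrawn from study treatment, not from the trial. Follow-up continues to day 28 and the patient is analysed in the originally randomised arm.
2. An SAE judged possibly related to study drug stops study drug. The patient goes to the institute protocol and is not re-randomised into the severe group. Barring only ribavirin-containing arms would not work: severe arms B and C both contain it, so only arm A would be left and there would be nothing to randomise.
3. Worsening attributed to COVID-19 follows the shift rule. Say which exclusions are checked again at that step, because an arm B patient shifted for disease progression could still draw arm C.

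The cost is a few sentences and a causality column in the Adverse Event Log, which has none now. No extra tests are needed.

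The downside is real. The causality call is open label and affects only non-severe arm B, because arm A receives no study drug. Entry to the severe group can therefore depend on the original arm. The non-severe comparison should for that reason stay by original randomisation. Recording the reason for each transfer by original arm would show the imbalance but not remove it.

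### Transfers who draw the hydroxychloroquine arm leave for institute care, so severe arm B is not comparable with arms A and C on safety once transfers are counted

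*Protocol*

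**What the plan says.** All of this is in the Protocol, Brief description of the proposal, mainly item (e).

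- **Transfer.** Under Treatment Schedule, a non-severe patient who fails to improve, or who shows signs of severity, moves on: "the patient will be shifted to the severity arm (S-group) of the clinical trial and again randomization will be done". New consent is required.
- **Exit rule.** The next sentence adds that "if intervention falls on HCQ arm, then it will be taken as end point reached and shifted to institute treatment protocol for further management". The flow diagram shows the transfer and second randomisation without this exception.
- **Severe arms.** A is standard treatment, B is hydroxychloroquine + ribavirin + standard treatment, and C is lopinavir-ritonavir + ribavirin + standard treatment.
- **Direct entry.** Patients who enter the severe group directly must meet listed criteria: "The patients will be categorised as severe based on the following criteria".
- **Analysis.** Statistical analysis states: "Primary analysis will include all patients (Intention to treat) and sub-group populations (per-protocol". It has no rule for transfers. Safety Outcomes names a grading table and events of interest but no analysis set.
- **Objective.** Objective 2 in item (b) is a safety and efficacy comparison of the three severe arms.
- **Case report form.** The severe form has a field for the previous regimen that lists both non-severe arms, so transfers are expected there.

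**The concern.** The exit rule acts on one severe arm only. A transfer drawn to A or C is treated and followed there. A transfer drawn to B receives none of B's drugs. The arms are balanced at the second randomisation and stop being comparable directly afterwards, by design.

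B-A is the only comparison of hydroxychloroquine + ribavirin with standard treatment in severe patients, and the protocol singles out arrhythmias, gastrointestinal events and myopathies. If transfers are counted where drawn, B contains patients never exposed to its drugs. If they are dropped from B, it holds direct entrants only, while A and C mix direct entrants with transfers.

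Those two kinds of patient can differ. Transfers may enter for non-improvement alone, without meeting a severe criterion. They have also passed a filter, because "If any serious adverse event is recorded, the participant will be withdrawn from the trial". Transfers from non-severe arm B bring earlier hydroxychloroquine + ribavirin with them.

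**Working it through.** **Inputs.** The rules above come from the protocol. It gives no sample size, allocation ratio, event rate, transfer rate or description of institute care, so there is no planned figure to reproduce and every number below is an assumption.

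- s: transfers as a share of each severe arm as randomised, 10/30/50%
- d: risk added by either combination, 15 points (true B-A = 15, true B-C = 0)
- e: risk added by institute care over standard treatment
- h: share of transfers from non-severe arm B, 0.5
- c: fraction of d carried over from non-severe arm B, 0 to 1
- pd, pt: baseline risk of direct entrants and of transfers

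Risks are additive.

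**1. Transfers counted where drawn, literal reading**

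A = (1-s)pd + s(pt + hcd)

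C = A + d

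B = (1-s)(pd + d) + s(pt + e + hcd)

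Hence B-A = d - s(d - e) and B-C = -s(d - e). The terms pd, pt and c cancel; e does not.

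| Case | Contrast | s = 10% | s = 30% | s = 50% |
|---|---|---|---|---|
| d = 15, e = 0 | B-A | 13.5 | 10.5 | 7.5 |
| d = 15, e = 0 | B-C | -1.5 | -4.5 | -7.5 |
| d = 5, e = 0 | B-A | 4.5 | 3.5 | 2.5 |
| d = 5, e = 0 | B-C | -0.5 | -1.5 | -2.5 |

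If institute care adds e = 5 points, then at s = 30% B-A = 15 - 0.3 x 10 = 12.0 and B-C = -3.0. If e = d, both biases are zero. If d = 0 and e = 0, there is no bias either.

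**2. Transfers counted where drawn, narrower reading**

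If only transfers from non-severe arm B leave, then with e = 0, B-A = d(1 - sh) = 14.3/12.8/11.3 and B-C = -shd = -0.8/-2.3/-3.8. The bias is half that of step 1.

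**3. Transfers left out of B only, literal reading**

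B = pd + d, so the same bias enters B-A and B-C: s(pd - pt) - shcd. At s = 30% the second term is 0.3 x 0.5 x 15c = 2.25c points.

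| pd - pt (points) | c = 0 | c = 0.5 | c = 1 |
|---|---|---|---|
| +10 | +3.0 | +1.9 | +0.8 |
| 0 | 0 | -1.1 | -2.3 |
| -10 | -3.0 | -4.1 | -5.3 |

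Over s = 10-50% the extremes are -5.0 - 3.75 = -8.75 (about -8.8) and +5.0 points. The bias is zero when pd = pt and c = 0. Under the narrower reading it is [sh(1-s)/(1-sh)](pd - pt) - shcd, which at s = 30% and pd - pt = +10 gives +1.2/+0.1/-1.0 for c = 0/0.5/1.

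**4. Exclusions applied again at the second enrolment**

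Exclusion 2 ("Patient already on antiretroviral therapy with Lopinavir-Ritonavir based regimen or on Hydroxychloroquine/Chloroquine or on Ribavirin") and exclusion 6 ("Receipt of any experimental treatment for 2019-nCoV (off-label, compassionate use, or trial related) within 30 days prior to participation in the present study") would bar transfers from non-severe arm B. Step 1 is then unchanged, and step 3 becomes s(pd - pt), up to 1/3/5 points either way. This cannot be combined with the narrower reading, because the exit rule would then apply to nobody.

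**5. Arm C against arm A**

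C - A = d in every case.

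**6. Precision**

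Assume 30 direct entrants per arm, so 30/(1-s) = 33.3/42.9/60 as randomised, with pd = pt = 5%, c = 0 and e = 0. Restricted to direct entrants, the standard error of B-A is sqrt(0.05 x 0.95/30 + 0.20 x 0.80/30) = 8.32 points.

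| Analysis | SE of B-A, s = 10/30/50% | Expected B-A / SE |
|---|---|---|
| Direct entrants only | 8.32 | 15/8.32 = 1.80 |
| Transfers counted where drawn | 7.71/6.45/5.11 | 1.75/1.63/1.47 |
| Transfers left out of B only | 8.22/8.03/7.83 | 1.82/1.87/1.92 |

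**The case against.** The strongest reply has four parts.

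- **The safety analysis set is not fixed here.** The intention-to-treat sentence concerns the primary analysis, and the frequency of serious adverse events is a secondary endpoint. A safety population is normally defined in the analysis plan, which is not at hand. This stands. A reader might infer that the protocol commits itself to understating arm B's harm, but the text does not go that far. The asymmetry, however, comes from an allocation rule in the protocol, and an ordinary as-treated safety set would only move the problem from step 1 to step 3.
- **Institute care is undescribed.** The dilution in step 1 requires care less toxic than arm B. This also stands, and it makes those figures conditional. B-C is better called biased than diluted, since a true difference can shrink, appear or grow.
- **The exit sentence may be meant for those who already failed hydroxychloroquine.** That is a sensible clinical reading. The text does not limit the rule in this way, nor does it exclude the reading. It would mean that arm B does have treated transfers, from non-severe arm A. The gap then concerns only transfers from non-severe arm B.
- **Dropping transfers from B may do no harm.** True when baseline risks are equal and nothing carries over. In that case the restriction costs some precision without removing any bias. The protocol gives no grounds for assuming either condition.

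**Conclusion.** The point holds in a conditional form and should be acted on. The exit rule makes severe arm B differ from A and C in how transfers are handled. This applies to all transfers on the literal reading and to those from non-severe arm B on the narrower one. Neither analysis that the protocol names, if applied to safety, then assures a clean B-A or B-C contrast. The sizes in the working illustrate what is possible under stated assumptions; they are not estimates for this trial.

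Two stronger conclusions are not supported. One is that leaving transfers out makes arm B look safer: the direction depends on case mix and carry-over, which the protocol does not determine. The other is that the whole severe comparison is compromised: A against C is unaffected, and nothing here implies bias in the non-severe stratum.

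**What to change.** 1. Make the B-A and B-C safety comparisons among patients whose first randomisation was in the severe group.
2. Tabulate transfers separately by prior non-severe arm, including those who drew the hydroxychloroquine arm and left.
3. State which transfers the exit rule covers, and whether exclusions 2 and 6 apply again at the second enrolment.
4. The A-C comparison may include transfers, stratified by prior non-severe arm.

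This takes a few lines of wording. The stratum and arm of each randomisation should come from the allocation record. The protocol mentions dynamic randomisation without saying what is recorded, so it should require this. The previous-regimen field on the severe form can serve only as a cross-check, because that form's arm labels differ from the design.

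The downside is a smaller severe safety set that describes only patients who present as severe. On the assumptions of step 6, the ability to detect harm is no worse than with transfers counted where drawn. It is slightly lower than with only B's transfers left out, and that small loss buys comparable arms.
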